### Trial status

HBI began in December 2012 at 40 churches in Enugu State, Nigeria. To date, we have recruited 2,000 participants of the expected 5,400. Participant recruitment will be completed in August 2013, with each participant followed though pregnancy and up to eight weeks post-delivery.

## Discussion

### Challenges and limitations

In the first few months of implementing the study, we encountered several ‘real world challenges’ that resulted in some redesign of the protocol as originally conceived.

### Church recruitment

One of the most common barriers to recruitment of churches to participate in clinical trials involves the suspicion with which faith-based organization views the scientific community. We had anticipated that this might impact our recruitment, but to our surprise, we had such a willingness and insistence to participate from the priests that the 200 churches in the four dioceses all wanted to participate in the study. They saw the program as an evangelical tool to encourage and increase the number of males who traditionally do not attend church services regularly. Pregnant women in churches that were not initially selected were reportedly going to close by churches that were participating in the program. To avoid the potential impact of unstructured participation, we used a spoke-and-hub approach to include all the churches. Each initially selected church acts as a coordinating hub for surrounding churches that follows the randomization group of their coordinating church. This provided an organized method of expanding the number of churches to accommodate the high uptake without disrupting the randomization and follow-up schedule in the study. Baby shower receptions were held at the coordinating churches, while recruitment occurs at each individual church.

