### Church recruitment and randomization

Recruitment occurred at the level of the churches and participants (in that order), while randomization occurred only at the church level. A total of 40 churches selected from four dioceses (the Anglican diocese of Enugu, the Catholic diocese of Enugu, the Anglican diocese of Oji-River, and the Catholic diocese of Agwu) were randomized to either the IG or the CG. All of the bishops who oversee churches in the proposed study areas had previously agreed to participate in this study and gave the study team access to speak to the priests under their dioceses. Randomization of churches occurred in 4 cohorts of 10 churches following random ranking. The churches were randomized in a 1:1 ratio to either the IG or CG. The sequence of randomization was generated by [name] and kept in a sealed opaque envelop away from the study sites in accordance with CONSORT guidelines
[45]. Once the sites had been recruited and baseline information on churches collected (*e.g.*, type, size of congregation), the sites were informed of their randomization group and assigned a code. Because of the nature of the intervention, it was impossible to blind the participants, community health nurses, lay health advisors, and study coordinators to the group assignment, but the test results cannot be influenced by the study coordinators.

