### Sample size and power analysis

The proposed study is a two-arm cluster randomized controlled trial with the church as the unit of randomization. Thus, there are two important sample size estimates: N, the number of pregnant women; and K, the number of churches, with the pregnant women nested within the K churches. We reviewed the total annual infant baptisms in churches located in Enugu and Oji-River for 2010 to estimate the potential number of pregnant women. Our review indicated that there were 20,700 infant baptisms conducted in 2010. Further analysis showed that in 2010, Enugu and Oji-River each contained about 50 churches that had 200 infant baptisms and 40 churches that had at least 100 infant baptisms (Table 
1).

**Table 1 T1:** Infant baptisms in churches

**Enugu Local Government Area**	**Oji-River Local Government Area**
Catholic Churches: 9,300 infant baptisms	Catholic Churches: 9,000 infant baptisms
Anglican Churches: 1,400 infant baptisms	Anglican Churches: 1,000 infant baptisms

Power calculations were performed using the module ‘Inequality Tests for Two Proportions in a Cluster-Randomized Design’ in PASS 11, which implements methods of Donner and Klar
[46]. That module approximates power for simple two-sample binomial tests for data collected in clusters with non-zero intra-cluster correlation (ICC). The Proc GLIMMIX analysis should have superior power since inclusion of covariates should reduce variability. For all three hypotheses, there will be 40 clusters (churches). For all three, there is an anticipated Control Group rate between 15% and 25%
[1,8]. The usual recommendation is to take ICC between 0.002 and 0.05; ICC as high as 0.10 is considered quite high. The PASS module chooses a cluster size (number of individuals per cluster), which determines the total sample size as cluster size X, no. of clusters. Table 
2 shows minimum detectable Intervention Group rates for various cluster sizes, Control Group rates, and ICC. The total sample size is driven by Secondary Hypothesis 2, where the CG rate should be around 0.20, and the intervention is expected to more than double the rate. From the preceding Table 

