### Statistical methods

All three hypotheses test for differences in two binomial proportions at follow-up. Clustering effects must be incorporated in the analysis since data collected on parishioners within the same church could be expected to exhibit correlation, while data collected on parishioners in different churches should exhibit minimal correlation. Generalized linear mixed models as implemented in PROC GLIMMIX in SAS 9.3
[47] provide a rich set of tools for analyzing such data. Data will be analyzed with that procedure using a logit link function and the binomial distribution. These are multilevel models allowing incorporation of covariates and confounders for the individual (such as age, household income, education level, previous HIV testing, last menstrual period, marital status, employment status, male’s partners’ previous HIV test results, and situational/contextual factors) and cluster-level (*i.e.*, church) covariates and confounders such as size of church and congregation type (Anglican or Catholic). For all three hypotheses, a preliminary (and similar) analysis will model the probability that an individual declines participation; any significant predictors from that model will be used in the main analysis to reduce confounding. Statistical significance will be set as p-value <0.05 and tests will be 2-sided.

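### The claim that the hub-and-spoke expansion left randomisation undisturbed is not supported: only the 40 hub churches were randomised, and the spokes inherited an arm that was already open

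*Protocol article*

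**What the plan says.** All references are to the protocol article.

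- **Sample size and power analysis** fixes the unit: "The proposed study is a two-arm cluster randomized controlled trial with the church as the unit of randomization".
- **Church recruitment and randomization** describes a sealed, opaque envelope and says: "Randomization of churches occurred in 4 cohorts of 10 churches following random ranking". After recruitment and collection of baseline church data, "the sites were informed of their randomization group and assigned a code". The Abstract confirms that the trial is unblinded and that churches know their group.
- **Trial status** has the trial starting at 40 churches in December 2012.
- **Challenges and limitations** places the redesign in the first few months of implementation.
- **Church recruitment** (Discussion) reports that all 200 churches in the four dioceses wanted to take part and that women from unselected churches were reportedly going to participating churches nearby. All churches were therefore included: "Each initially selected church acts as a coordinating hub for surrounding churches that follows the randomization group of their coordinating church". Women are recruited at each church, and baby showers are held at the hub. The section describes the scheme as a way of "expanding the number of churches to accommodate the high uptake without disrupting the randomization and follow-up schedule in the study".
- **Statistical methods** treats the church as the cluster and gives church size and congregation type as examples of cluster-level covariates.

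**The concern.** The concealed sequence protected the allocation of 40 churches. It could not protect the allocation of churches that joined later, because the arm they would receive was by then public. The arms also differ visibly: control showers have no game and no free on-site laboratory tests (Description of the control condition/usual care).

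If the choice of hub was influenced by the hub's arm for even some spokes, churches with better access or more motivated congregations could be over-represented in one arm. That imbalance would be read as an effect of the intervention on women's testing, on partner testing and on PMTCT completion. Adjusting for church size and denomination would not remove it. Individual covariates such as previous HIV testing and education would help only in part.

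The article tells the reader that randomisation is intact, so a reader has no reason to look for this.

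**Working it through.** **1. Churches without their own random allocation.** Inputs: 40 randomised; 200 in the four dioceses; all included.

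- Spokes = 200 − 40 = 160.
- Share of churches = 160/200 = 80%, on average 160/40 = 4 spokes per hub.

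The 160 is inferred. It assumes that the 40 hubs are among the 200 and that every other church joined.

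**2. Share of women recruited at spokes.** Counting churches gives 80%. The planned hubs were mostly large, so a count by baptisms is lower. Each arm was to have 15 churches with 200 baptisms a year and 5 with 100:

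- Hub baptisms = 30 × 200 + 10 × 100 = 7,000.
- Area total (Table 1) = 9,300 + 9,000 + 1,400 + 1,000 = 20,700.
- Hub share = 7,000/20,700 = 34%; spoke share about 66%.

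This assumes that the 20,700 covers the same 200 churches. Women enrolled before the expansion would lower the share further.

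**3. Possible shift in the arm difference.** Shift = spoke share × difference in underlying testing tendency between intervention-attached and control-attached spokes. The documents give no such difference; 5 to 10 points is an assumption.

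| Spoke share | 5 points | 10 points |
|---|---|---|
| 66% | 3.3 | 6.6 |
| 80% | 4.0 | 8.0 |

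**4. Scale for comparison.** Table 2, control rate 0.20, cluster size 50, ICC 0.05, gives a minimum detectable rate of 0.30. To reproduce it:

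- Design effect = 1 + 49 × 0.05 = 3.45.
- Effective n per arm = 20 × 50/3.45 = 290.
- SE = √[(0.20 × 0.80 + 0.30 × 0.70)/290] = 0.0357.
- 0.10/0.0357 − 1.96 = 0.84, which is 80% power.

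The article does not state the power, but this form at 80% reproduces all 45 cells of Table 2 within 0.006. The 10 points is a detectable difference from one cell, not an expected effect. It shows only that a shift of 3 to 8 points would not be negligible.

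**5. What the cluster is now.** With 2,700 women, control rate 0.20, ICC 0.05, 80% power and the pooled form of the test:

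- 40 hub clusters of 67.5 women: design effect 4.325, effective n 312 per arm, detectable rate 0.297.
- 200 churches of 13.5 treated as independently randomised: design effect 1.625, effective n 831 per arm, detectable rate 0.258.

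The second figure overstates the precision, because only 40 units were randomised.

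**6. Size of a hub-only set.**

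- Planned rates: (15 × 16 + 5 × 8) × 5 = 1,400 per arm, against 1,350 needed.
- The article's lower case of 12 a month at large churches: (15 × 12 + 5 × 8) × 5 = 1,100 per arm.
- HIV-infected women, both arms, at 6% prevalence and 10% dropout: 2,800 × 0.06 × 0.9 = 151, or 2,200 × 0.06 × 0.9 = 119, against a target of 140.

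**The case against.** The strongest reply is that inheriting a hub's arm is not in itself a departure from randomisation. The hubs were randomised. If spokes were attached by location alone, a hub with its spokes is one randomised cluster and the comparison is valid. The stated criterion is geographic, no passage says that churches chose their hub, and a journal article may leave the attachment rule to the full protocol. This stands. The absence of a detailed rule is not the point. The point is the flat assurance, which holds only if attachment did not depend on arm, and the article does not say so.

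Three stronger readings are tempting, and the documents do not support them.

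- **The spoke comparison is non-randomised, or biased.** The text shows an opportunity for selection, not that it happened.
- **Keener churches went to the intervention arm.** All 200 wanted to join and all were included, so keenness did not decide entry. Only the choice of hub could be affected. It is also not stated what defined the four randomisation cohorts, so how often a spoke lay near hubs of both arms is unknown.
- **The primary analysis should be restricted to the 40 hubs.** Women were reportedly already going from unselected to participating churches, so that set is not clean either. The change would also alter the primary set of an open trial with 2,000 of an expected 5,400 participants recruited, and would depart from the stated intent-to-treat analysis.

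**Conclusion.** The concern holds as a matter of an unsupported assurance and an unaddressed risk. Only 40 churches were randomised. About 160 others received their arm by attachment, during implementation and with hub arms open. That attachment followed disclosure is pieced together from the Abstract and the sections on randomisation, trial status and challenges; no single sentence says it.

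The possible shift is about 3 to 8 percentage points. This rests on an assumed 5 to 10 point difference between spokes in the two arms and on a spoke share of women between 66% (baptisms) and 80% (churches). If attachment was independent of arm, the expected shift is zero. The primary outcome and both secondary outcomes rest on the same contrast, so the point affects what the trial can conclude.

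**What to change.** 1. **Replace the assurance.** For example: *Only the 40 coordinating churches were randomised. Surrounding churches took the arm of their coordinating church; validity for these churches depends on attachment having been independent of arm.* Add how and when attachments were made.
2. **Keep the full hub-plus-spoke set as the primary intent-to-treat analysis**, and define the hub with its spokes as the randomised cluster in the mixed model, giving 40 clusters.
3. **Audit the attachments.** Someone without the arm list applies a nearest-hub rule to every spoke. Flag the exceptions and report their number by arm.
4. **Prespecify a key sensitivity analysis** of women recruited at the 40 originally randomised churches, limited where possible to those enrolled before the expansion or whose own church is the hub.

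The cost is a flag for hub or spoke church, the enrolment date and home church where recorded, a desk check of about 160 attachments, and one further run of the same model. The downside is precision. The hub-only set is 1,400 per arm at planned rates, which needs near-complete uptake at churches averaging 16 baptisms a month, and 1,100 at the lower rate. PMTCT completion suffers most: about 119 HIV-infected women at the lower rate, close to the row of Table 2 for 120, where the detectable rate is 0.44 against 0.20 at ICC 0.05. Limiting the set to women enrolled before the expansion would reduce it further, by an amount the article does not allow one to calculate.

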### Participant recruitment

Due to the high uptake of the program by churches and subsequent uptake by pregnant women, Sundays initially reserved for baby showers also became recruiting days. This initially overwhelmed the study team. Activities initially planned for an estimated 25 participating pregnant women and their male partners ended up being attended by 100 potential participants. The study team initially ran out of supplies of forms, mama packs, and blood sample collection kits. It took a couple of months before the study team was able to closely estimate attendance at baby shower programs. Initially, some pregnant women were turned away as consent forms were exhausted.

### Data collection

Although the questionnaire was constructed at a sixth grade reading level, administration of the questionnaire became very time consuming as we encountered a rather large number of individual participants who could not read English or the local language. The utilization of local church-based facilitators became very helpful in providing basic translation of information.

## Conclusions

The proposed study will test a congregation-based intervention that uses a family-centered, culturally-appropriate approach that relies on a widely distributed infrastructure (religious institutions). If successful, this approach could become a platform for multiple interventions aimed at improving the quality of maternal child health services especially in hard-to-reach communities.

## Abbreviations

HBI: Healthy beginning initiative; PMTCT: Prevention of mother-to-child HIV transmission.
